## 7.4 Statistical Analyses for Pharmacokinetics

---

Plasma concentrations and PK parameter values for ABBV-467 will be tabulated for each subject, and dose level. Summary statistics will be computed for each sampling time and each PK parameter.

Details on the statistical analyses for PK will be provided in the SAP.

## 7.5 Statistical Analyses for Safety

---

Safety analyses will be performed on the all-treated subjects. Subjects will be assigned to a treatment group based on the treatment received. The safety of ABBV-467 will be assessed by evaluation of study drug exposure, AEs, SAEs, and deaths, as well as changes in laboratory and vital sign parameters.

### Analysis of Adverse Events

Analyses of AEs will include only treatment-emergent events. The number and percentage of subjects experiencing treatment-emergent AEs will be tabulated according to the primary Medical Dictionary for Regulatory Activities (MedDRA) system organ class (SOC) and MedDRA preferred term. Subjects reporting more than 1 AE for a given MedDRA preferred term will be counted only once for that term. Subjects reporting more than one type of AE within a MedDRA SOC will be counted only once for that SOC. Subjects reporting more than one type of AE will be counted only once in the overall total.

SAEs, drug-related AEs, AEs leading to death, dose interruption and dose modification as applicable, study treatment discontinuation, and study discontinuation will be summarized using the same methods as described above.

### Analysis of Laboratory Data

Baseline values and changes from baseline will be summarized for each scheduled post-baseline visit for laboratory data as applicable. If more than one measurement exists for a subject on a particular day, an

arithmetic average will be calculated. This average will be that subject's measurement for that day. For subjects that do not have any post-baseline measurements, only their baseline values will be summarized.

Descriptive statistics will include the mean, standard deviation, and median for baseline, and mean, standard deviation, median, minimum, and maximum for change from baseline for each scheduled post-baseline visit.

### Analysis of Vital Signs

Baseline values and changes from baseline will be summarized for each scheduled post-baseline visit for vital signs data as applicable using methods similar to the analysis of laboratory data.

Details on the statistical analyses for safety will be provided in the SAP.

## 7.6 Multiplicity Adjustment and Overall Type I Error Control

---

Not applicable.

## 7.7 Sample Size Determination

---

A total of approximately 108 subjects will be enrolled in this study. In the dose-escalation component, the number of subjects will depend upon the occurrences of DLT events as specified in the allocation rules for BOIN design. Including a minimum of 6 subjects treated during dose escalation at what is ultimately declared the RP2D, it is estimated that approximately 30 subjects each will be treated in Part A and Part C (approximately 60 total).

The expansion component will target enrollment of 20 response-evaluable subjects (with a maximum of 24 subjects enrolled regardless of response evaluability) each into Parts B and D (up to 48 enrolled total) to further evaluate the safety profile, and preliminarily evaluate efficacy, of ABBV-467 at RP2D. Subjects will be considered response-evaluable if they have received at least 1 dose of ABBV-467 and have died, or exited the study due to progressive disease, or had at least 1 post-baseline response assessment per the indication-specific response criteria. Subjects who die or exit for progressive disease, prior to their first baseline assessment, will be considered to have not responded to the therapy.

With a sample size of 24 subjects, the probability to observe at least 1 occurrence of AE is  $\geq 92\%$  if the true incidence of the respective AE rate is  $\geq 10\%$ .

No formal hypothesis testing is planned for this first-in-human study; preliminary assessment of efficacy is a secondary objective of this study. [Table 5](#) provides the lower bound of a one-sided 80% CI corresponding to various observed response rates assuming a total of 20 response-evaluable subjects in each cohort. For example, if a 25% response rate is observed, the lower bound of a one-sided exact CI will exclude 15% (or lower) rates of response, providing some preliminary assessment of efficacy.

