### 7.2 Definition for Analysis Populations

---

Efficacy and safety analyses will be performed on the all-treated population which comprises all subjects who receive at least 1 dose of study drug. The PK population is defined as subjects who received at least 1 dose of study drug and have at least 1 valid post-baseline PK data; PK analyses will be based on the PK population.

Details on the analysis population definitions will be provided in the SAP.

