### 7.3 Statistical Analyses for Efficacy

---

Efficacy analysis will be performed separately for subjects with R/R MM and R/R AML.

Efficacy for R/R MM subjects will include analyses of ORR (PR + VGPR + CR + sCR), DOR, and CBR.

Efficacy for R/R AML subjects will include analyses of CRc rate (CR + CRi), CRh, ORR (CRc + PR), and DOR.

Exploratory efficacy analysis includes overall survival (OS) for both R/R MM and R/R AML.

For Parts A and C, efficacy data will be listed for each dose level.

For Parts B and D, efficacy analyses will be performed by cohort for the all-treated population. For binary endpoints (such as ORR, CBR, CRc, CRh), the estimated proportion and the associated 2-sided 90% Clopper-Pearson (exact) confidence intervals (CIs) will be provided for each cohort. DOR will be defined as the time between date of first response and the first occurrence of progression or death from any cause, whichever occurs first. Only responders will be included in the analysis of DOR. DOR for subjects without DOR events at the time of analysis will be censored at the date of last disease assessment. If a subject receives a new anti-cancer therapy, DOR will be censored at the date of last disease assessment prior to the start of the new therapy. DOR will be summarized using the Kaplan-Meier method. The median DOR and its associated 2-sided 90% CIs will be provided for each cohort. For R/R MM subjects, DOR will be analyzed among subjects who achieved PR, VGPR, CR or sCR. For R/R AML subjects, DOR will be analyzed among subjects who achieved CRc or PR. OS will be defined as the time from the date of the first dose of study treatment to the date of death. For subjects who are not deceased, the data will be censored at the last known alive date. OS will be summarized using the Kaplan-Meier method. The median OS and its associated 2-sided 90% CIs will be provided.

Additional details on the efficacy analyses are provided in the SAP.

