**Table 5. Exact 1-Sided 80% Confidence Intervals from Various Response Rates**

| Cohort Size (n) | # of Responders | Observed Response Rate a | Exact 80% Confidence Interval |
|-----------------|-----------------|-------------------------------------|-------------------------------|
| 20              | 5               | 25%                                 | (0.158, 1)                    |
|                 | 6               | 30%                                 | (0.201, 1)                    |
|                 | 7               | 35%                                 | (0.245, 1)                    |
|                 | 8               | 40%                                 | (0.291, 1)                    |
|                 | 10              | 50%                                 | (0.384, 1)                    |

AML = acute myeloid leukemia; CR = complete remission; CRi = complete remission with incomplete blood count recovery; MM = multiple myeloma; ORR = overall response rate

a. CR/CRi for AML cohort; ORR for MM cohort.

Note: Cohort size refers to the number of response-evaluable subjects.

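### Table 5's exclusion of 15% at 5/20 holds for its one-sided 80% bound, but not for the two-sided 90% interval that Section 7.3 says Parts B and D will report

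*Protocol*

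**What the plan says.** Section 7.7 (Sample Size Determination) says that its Table 5 "provides the lower bound of a one-sided 80% CI corresponding to various observed response rates". Each cohort is taken to have 20 subjects who can be evaluated for response. The worked example is that "if a 25% response rate is observed, the lower bound of a one-sided exact CI will exclude 15% (or lower) rates of response". Table 5 lists 5, 6, 7, 8 and 10 responders out of 20, with lower bounds 0.158, 0.201, 0.245, 0.291 and 0.384 and an upper limit of 1 throughout. Its footnote fixes the denominator: "Note: Cohort size refers to the number of response-evaluable subjects".

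Section 7.3 (Statistical Analyses for Efficacy) sets out what will be reported. The population is given first: "For Parts B and D, efficacy analyses will be performed by cohort for the all-treated population". As to the interval for binary outcomes such as response rates, "the estimated proportion and the associated 2-sided 90% Clopper-Pearson (exact) confidence intervals (CIs) will be provided for each cohort". Section 7.2 defines the "all-treated population which comprises all subjects who receive at least 1 dose of study drug".

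Section 7.7 also caps each expansion cohort at 24 enrolled subjects whether or not they are evaluable, states that no formal hypothesis test is planned, and treats efficacy as a secondary, preliminary assessment.

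**The concern.** The protocol describes two intervals for the same response rate and does not connect them. The planning interval leaves 20% in the lower tail and uses response-evaluable subjects. The reporting interval leaves 5% in the lower tail and uses everyone dosed. Section 7.7 does not say that its interval is for planning only, and Section 7.3 does not say that a one-sided 80% bound will be shown as well.

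Table 5 and its example are the only efficacy argument given for the cohort size. Someone who takes the example at face value will expect a cohort with 5 responders in 20 to be reported with 15% ruled out. The interval that the protocol commits to reporting would run down to about 10%. The stated precision is therefore better than that of the planned analysis.

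**Working it through.** **Inputs.** Lower-tail probability a = 0.20 for the one-sided 80% bound (Section 7.7, Table 5); a = 0.05 in each tail for the two-sided 90% interval (Section 7.3). Denominators: 20 response-evaluable (Section 7.7), and all-treated up to the cap of 24 (Sections 7.2, 7.3, 7.7). Reference rate: 15% (Section 7.7 example).

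**Formulas.** For x responders out of n, the exact lower limit is the a-quantile of Beta(x, n − x + 1), and the exact upper limit is the (1 − a)-quantile of Beta(x + 1, n − x).

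**Step 1: reproduce Table 5, then apply the Section 7.3 interval at the same n = 20.**

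| Responders / 20 | Table 5 | One-sided 80% lower, recomputed | Two-sided 90% (Section 7.3) |
|---|---|---|---|
| 5 (25%) | 0.158 | 0.1584 | 0.104 to 0.456 |
| 6 (30%) | 0.201 | 0.2013 | 0.140 to 0.508 |
| 7 (35%) | 0.245 | 0.2454 | 0.177 to 0.558 |
| 8 (40%) | 0.291 | 0.2906 | 0.217 to 0.606 |
| 10 (50%) | 0.384 | 0.3840 | 0.302 to 0.698 |

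All five Table 5 bounds reproduce. With every subject evaluable and n exactly 20, the Section 7.3 interval contains 15% at 5 and at 6 responders, and first lies above it at 7.

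**Step 2: check through the binomial tail.** An exact lower limit with tail a exceeds 0.15 exactly when P(X ≥ x | n, 0.15) < a. For n = 20:

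- P(X ≥ 5) = 0.170: below 0.20, above 0.05.
- P(X ≥ 6) = 0.067: below 0.20, above 0.05.
- P(X ≥ 7) = 0.022: below both.

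So 5/20 passes the Table 5 criterion and fails the Section 7.3 one, in agreement with Step 1.

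**Step 3: separate the denominator from the confidence level.** Keep the one-sided 80% bound and change only n.

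- 5 responders held fixed: n = 20, 0.158; n = 21, 0.151; n = 22, 0.144; n = 23, 0.137; n = 24, 0.131. Exclusion of 15% is lost from n = 22.
- Rate held at 25%: 6/24 gives 0.167, which still excludes 15%.

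The denominator therefore does harm only when extra treated subjects enter as non-responders. On the two-sided 90% interval, 6/24 has a lower limit of 0.115; the fall from 0.167 comes entirely from the confidence level.

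**Step 4: where the Section 7.3 lower limit first exceeds 15%.**

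| n all-treated | Lower limit, 6 responders | 7 responders | 8 responders | First count above 15% |
|---|---|---|---|---|
| 20 | 0.140 | 0.177 | 0.217 | 7 (35%) |
| 21 | 0.132 | 0.168 | 0.206 | 7 (33%) |
| 22 | 0.126 | 0.160 | 0.196 | 7 (32%) |
| 23 | 0.120 | 0.152 | 0.186 | 7 (30%) |
| 24 | 0.115 | 0.146 | 0.178 | 8 (33%) |

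**The case against.** The best defence is that neither section is false. Table 5 names its interval in the title, the sentence before the example gives the 80% level, and the example itself says one-sided. Two confidence levels applied to the same data may disagree about 15% without contradicting each other, and a trial may plan with one interval and report another. This stands as far as it goes. A reader might infer that Table 5 is miscalculated; it is not, and all five bounds reproduce.

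Second, nothing is decided on this figure. Section 7.7 rules out formal testing, Section 7.6 lists type I error control as not applicable, and no go/no-go or stopping rule mentions 15% or 5/20. A reader might take the 17% chance of 5 or more responders at a true rate of 15% as an inflated false-positive rate, but the trial runs no test to which it would belong. The cohort size also has a separate safety argument, which is correct: 1 − 0.9^24 = 0.920 for seeing at least one event with a true rate of 10%. This limits the seriousness of the point but does not remove it.

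Third, the two populations may barely differ. Response-evaluable includes treated subjects who died, left for progression or had one post-baseline assessment, and 24 is a cap rather than the planned n. A reader might infer that moving to the all-treated set by itself defeats the example; at a held rate of 25% it does not (6/24, 0.167).

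Finally, the SAP is not at hand and might add a one-sided bound or a response-evaluable summary. It therefore cannot be said that no reported analysis will have the Table 5 property. But both intervals and both populations are already fixed in the protocol, and the protocol leaves them unreconciled.

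**Conclusion.** The point holds as an inconsistency between Sections 7.7 and 7.3. Table 5 is right for the interval it names, but that is not the interval the protocol commits to reporting for Parts B and D. At the example's own result, 5/20, the lower limit is 0.104 rather than 0.158, and 15% is not excluded. At n = 20 the gap is two responders: 7 (35%) instead of 5 (25%). This conclusion needs only the two stated confidence levels and assumes that all 20 subjects are evaluable. Any further loss from the all-treated denominator assumes that some treated subjects are not response-evaluable; for example, 5 responders among 22 treated give 0.144 even on the one-sided 80% bound.

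It is a moderate consistency correction. It affects how the precision of a secondary, preliminary efficacy assessment is described. No patient count, decision rule or primary objective depends on it.

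**What to change.** Preferred: rebuild Table 5 with two-sided 90% Clopper-Pearson limits on the all-treated set. For n = 20, use the last column of the first table under the working. Add n = 24: 5 responders, 0.086 to 0.389; 6, 0.115 to 0.435; 7, 0.146 to 0.479; 8, 0.178 to 0.521; 10, 0.246 to 0.603. Change the title and the footnote on cohort size to match. Replace the 25%-excludes-15% example with a statement that the lower limit first exceeds 15% at 7 responders for n = 20 to 23 and at 8 for n = 24, worded as precision and explicitly not as a decision threshold.

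Alternative: keep Table 5 and add a sentence to Section 7.3 that the one-sided 80% exact bound on response-evaluable subjects will be reported alongside the two-sided 90% interval, with a cross-reference in Section 7.7.

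The cost is one recomputed table or one added sentence. No extra patients are needed. Under the preferred option, the stated precision becomes less favourable.

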**Table 5. Exact 1-Sided 80% Confidence Intervals from Various Response Rates**

| Cohort Size (n) | # of Responders | Observed Response Rate a | Exact 80% Confidence Interval |
|-----------------|-----------------|-------------------------------------|-------------------------------|
| 20              | 5               | 25%                                 | (0.158, 1)                    |
|                 | 6               | 30%                                 | (0.201, 1)                    |
|                 | 7               | 35%                                 | (0.245, 1)                    |
|                 | 8               | 40%                                 | (0.291, 1)                    |
|                 | 10              | 50%                                 | (0.384, 1)                    |

AML = acute myeloid leukemia; CR = complete remission; CRi = complete remission with incomplete blood count recovery; MM = multiple myeloma; ORR = overall response rate

a. CR/CRi for AML cohort; ORR for MM cohort.

Note: Cohort size refers to the number of response-evaluable subjects.

## 8 ETHICS

### 8.1 Independent Ethics Committee/Institutional Review Board

The protocol, informed consent form(s), recruitment materials, and all subject materials will be submitted to the IEC/IRB for review and approval. Approval of both the protocol and the informed consent form(s) must be obtained before any subject is enrolled. Any amendment to the protocol will require review and approval by the IEC/IRB before the changes are implemented to the study. In addition, all changes to the consent form(s) will be IEC/IRB approved.

### 8.2 Ethical Conduct of the Study

The study will be conducted in accordance with the protocol, Operations Manual, ICH guidelines, applicable regulations, and guidelines governing clinical study conduct and the ethical principles that have their origin in the Declaration of Helsinki. Responsibilities of the investigator are specified in [Appendix B](#).

### 8.3 Subject Confidentiality

To protect subjects' confidentiality, all subjects and their associated samples will be assigned numerical study identifiers or "codes." No identifiable information will be provided to AbbVie.

## 9 SOURCE DOCUMENTS AND CASE REPORT FORM COMPLETION

The investigator is responsible for ensuring the accuracy, completeness, legibility, and timeliness of the data reported. All source documents should be attributable, legible, contemporaneous, original,

accurate, and complete to ensure accurate interpretation of data. Clinical site monitoring is conducted to ensure that the rights and well-being of human subjects are protected, that the reported trial data are accurate, complete, and verifiable, and that the conduct of the trial is in compliance with the currently approved protocol, ICH Good Clinical Practice (GCP), and applicable local regulatory requirement(s).

## 10 DATA QUALITY ASSURANCE

AbbVie will ensure that the clinical trial is conducted with a quality management system that will define quality tolerance limits in order to ensure human subject protection and reliability of study results. Data will be generated, documented, and reported in compliance with the protocol, ICH GCP, and applicable regulatory requirements.

## 11 COMPLETION OF THE STUDY

The end-of-study is defined as the date of the last subject's last visit or date of the last follow-up contact, whichever is later.

## APPENDIX A. STUDY SPECIFIC ABBREVIATIONS AND TERMS

| Abbreviation       | Definition                                                                                          |
|--------------------|-----------------------------------------------------------------------------------------------------|
| AE                 | adverse event                                                                                       |
| ALT                | alanine aminotransferase                                                                            |
| AML                | acute myeloid leukemia                                                                              |
| AST                | aspartate aminotransferase                                                                          |
| AUC                | area under the plasma concentration-time curve                                                      |
| AUC t   | area under the plasma concentration-time curve from time 0 to time of last measurable concentration |
| BCL-2              | B-cell lymphoma-2                                                                                   |
| BCL-X L | B-cell lymphoma - extra large                                                                       |
| BOIN               | Bayesian optimal interval                                                                           |
| C                  | Cycle                                                                                               |
| CBR                | clinical benefit rate                                                                               |
| CI                 | confidence interval                                                                                 |
| CL                 | clearance                                                                                           |
| C max   | maximum observed plasma concentration                                                               |
| CR                 | complete remission                                                                                  |
| CRc                | composite complete remission                                                                        |
| CrCl               | creatinine clearance                                                                                |
| CRh                | complete remission with partial hematologic recovery                                                |
| CRI                | complete remission with incomplete blood count recovery                                             |
| CT                 | computed tomography                                                                                 |
| CTCAE              | Common Terminology Criteria for Adverse Events                                                      |
| CVC                | central venous catheter                                                                             |
| D                  | Day                                                                                                 |
| DLT                | dose-limiting toxicity                                                                              |
| DOR                | duration of response                                                                                |
| ECG                | electrocardiogram                                                                                   |
| ECOG               | Eastern Cooperative Oncology Group                                                                  |
| eCRF               | electronic case report form                                                                         |
| ELN                | European Leukemia Net                                                                               |
| FFPE               | formalin-fixed paraffin-embedded                                                                    |

| Abbreviation | Definition                                                                                                            |
|--------------|-----------------------------------------------------------------------------------------------------------------------|
| FLC          | free light chain                                                                                                      |
| GCP          | Good Clinical Practice                                                                                                |
| HED          | human equivalent dose                                                                                                 |
| HNSTD        | highest non-severely toxic dose                                                                                       |
| ICH          | International Conference on Harmonisation of Technical Requirements for Registration of Pharmaceuticals for Human Use |
| IEC          | Independent Ethics Committee                                                                                          |
| IMP          | Investigational Medicinal Product                                                                                     |
| IMWG         | International Myeloma Working Group                                                                                   |
| IRB          | Institutional Review Board                                                                                            |
| IRT          | interactive response technology                                                                                       |
| IUD          | intrauterine device                                                                                                   |
| IUS          | Intrauterine hormone-releasing system                                                                                 |
| IV           | intravenous                                                                                                           |
| IWG          | International Working Group                                                                                           |
| MCL-1        | myeloid cell leukemia-1                                                                                               |
| MedDRA       | Medical Dictionary for Regulatory Activities                                                                          |
| MM           | multiple myeloma                                                                                                      |
| MRD          | minimal residual disease                                                                                              |
| MRI          | magnetic resonance imaging                                                                                            |
| MTD          | maximum tolerated dose                                                                                                |
| NCI          | National Cancer Institute                                                                                             |
| OBD          | optimal biological dose(s)                                                                                            |
| ORR          | overall response rate                                                                                                 |
| PD           | pharmacodynamic                                                                                                       |
| PET          | positron emission tomography                                                                                          |
| PG           | pharmacogenetics                                                                                                      |
| PK           | pharmacokinetic                                                                                                       |
| PR           | partial response                                                                                                      |
| RP2D         | recommended Phase 2 dose                                                                                              |
| R/R          | relapsed/refractory                                                                                                   |
| SAE          | serious adverse event                                                                                                 |
| SAP          | statistical analysis plan                                                                                             |

| Abbreviation | Definition                                    |
|--------------|-----------------------------------------------|
| sCR          | stringent complete response                   |
| SOC          | system organ class                            |
| SPEP         | serum protein electrophoresis                 |
| SUSAR        | suspected unexpected serious adverse reaction |
| TA MD        | Therapeutic Area Medical Director             |
| TLS          | tumor lysis syndrome                          |
| ULN          | upper limit of normal                         |
| UPEP         | urine protein electrophoresis                 |
| VGPR         | very good partial response                    |

